### Analysis

#### Feasibility and clinical outcomes

On the completion of the study, the data will be cleaned and analysed. Recruitment rate, retention and attrition are simple percentages of those recruited. The feasibility criteria (willingness to be recruited to the study, study retention (< 30% drop out), compliance (80%, daily percentage of exercises undertaken averaged over the intervention period), absence of adverse incidents and acceptability of intervention) will be used to establish whether it is feasible to progress to a larger-scale multi-centre randomised controlled trial. There will be comparisons between the three arms of the study. Non-parametric tests will be utilised to compare between the groups. Improvements in FOIS, TWST and TUAG will use parametric tests to compare between-group and within-subject changes.

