**Methods:**

We will recruit 60 medically stable patients over the age of 75 years who have been admitted with a diagnosis of pneumonia to the acute frailty wards at two participating hospitals in the UK. Study participants will be randomised into one of three groups: standard care, low intensity (once daily) CTAR-SwiFt exercise or high intensity (twice daily) CTAR-SwiFt exercises. The intervention period will last for 12 weeks, the final follow-up assessment will be conducted at 24 weeks. We will assess the feasibility outcomes, including rates of participant recruitment and retention, compliance with the exercise regime and adverse incidents. Additionally, we will assess the usability and acceptability of the intervention device and the performance of different clinical outcome measures (e.g. chin tuck strength, Functional Oral Intake Scale, SWAL-QOL, EQ-5D and swallow speed). A sub-sample of study participants will complete videofluoroscopic assessments of swallowing function before and after the intervention to evaluate the physiological changes (e.g. bolus flow rates, laryngeal elevation, base-of-tongue retraction).

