### Recruitment

All consecutive patients will be identified and screened in the acute frailty wards of the participating hospitals. The responsible medical team will identify the patients to the research team, who will be based in the ward. Identified patients will be screened against study eligibility criteria by the research team, prior to consent being sought.

Consent will be obtained by either the research staff or the responsible medical consultant. All patients participating in the study will be asked to provide informed consent. A patient information sheet will be provided prior to consent being sought. Participants will be given at least 48 h to consider whether they wish to be involved in the study.

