#### Safety/adverse events

Any adverse event (clinical or device-related) will be reported to the study co-ordinator and/or chief investigator according to Good Clinical Practice (GCP) and using a standard reporting form. A description of the adverse event and the outcome to the event will be recorded.

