### Control condition

One-third of the participants will be randomised to the control condition, which consists of the usual treatment (Fig. 1). Participants in the control group will undergo monthly MCTS assessments as participants in the intervention groups but will not conduct daily CTAR-SwiFt exercises.

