### Outcomes

Outcomes include feasibility and acceptability outcomes to inform the feasibility of conducting a definitive trial, as well as relevant clinical outcomes for future prospective sample size calculation for a definitive trial:Recruitment rates across two NHS hospital sites assessed using the number recruited per month and the total in the study period, recorded using trial management software.Willingness to be recruited to the study assessed using the number of people who refuse and their reasons for refusing, recorded using trial management software.Study retention (< 30% drop out) assessed using the number not completing the study relative to the number agreeing to participate, recorded using trial management software.Compliance: 80% of exercises undertaken (daily percentage averaged over the intervention period), monitored via the CTAR-SwiFt Android application which records exercise data for all sessions completed.The absence of adverse incidents assessed, using the number of reports recorded in trial management software.Acceptability of intervention, assessed using a 5-point questionnaire.Mechanics of swallowing, assessed using VF (reduced pharyngeal transit time, reduced residue post swallow).Aspiration prevention, assessed by analysing laryngeal movement, UES opening and tongue base retraction as visualised on VF.Swallow speed assessed using the Timed Water Swallow Test (TWST; time taken to drink 90 ml of water).Ease of use of the CTAR-SwiFt feedback ball, assessed using verbal feedback and a usability questionnaire.Swallowing ability assessed using FOIS, as completed by the medical staff.Dysphagia-related QoL, assessed using the SWAL-QOL questionnaire.Health-related QoL, assessed using the EQ-5D questionnaire.Strength and mobility assessed using the TUAG test. Participants must stand from sitting, walk 3 m, then turn around, walk back to the chair and sit down again.

Study assessments are conducted monthly, with all measures being completed at baseline, 12 weeks and 24 weeks (Table 1).

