### Sample size justification

This is a feasibility study, and as such, it is not powered to detect a statistically significant intervention effect. Sixty participants will be recruited, which was considered to be adequate to identify the possibility of progressing to a larger definitive study and is a generally recommended sample size for feasibility studies [21]. The objective measures, process mapping and qualitative data collected will aid in that decision.

The study is aiming to recruit 60 patients, at a minimum recruitment rate of 2 participants per site per month.

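### The progression criterion of zero adverse incidents has no limit by relatedness, arm or number, so it would mostly reflect background illness, and it does not match the safety standard in the Discussion

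*Protocol article*

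**What the plan says.** Three places in the protocol article bear directly on the criterion.

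- **Analysis, Feasibility and clinical outcomes.** Five feasibility criteria are named. Retention and compliance carry explicit tolerances (under 30% drop-out, 80% of exercises). The safety criterion carries none: "absence of adverse incidents and acceptability of intervention) will be used to establish whether it is feasible to progress" to a larger trial.
- **Outcomes.** The measurement is a count: "The absence of adverse incidents assessed, using the number of reports recorded in trial management software".
- **Safety/adverse events.** What must be reported is broad: "Any adverse event (clinical or device-related) will be reported to the study co-ordinator" and/or the chief investigator. No arm is exempted.

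Two other places describe the same decision differently. The last paragraph of the Discussion before the Conclusion rests it on feasibility outcomes together with evidence that the intervention is safe and potentially effective. The Sample size justification says that objective measures, process mapping and qualitative data will help to decide. No section says how the criteria are combined, or what happens if one of them fails.

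**The concern.** A safety criterion for progression should separate harm from the exercise ball from the illness that participants would have had anyway. This one does not. It counts reports whatever their cause and whichever arm they come from, and its only passing value is zero.

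The population makes that serious. Participants are frail, mostly over 75, "admitted with a diagnosis of pneumonia" and "screened in the acute frailty wards of the participating hospitals". The article itself expects illness during follow-up: it hopes that the intervention will lead to fewer chest infections and hospital admissions, which presupposes that these occur. One such event in a usual-care participant would, on the literal reading, breach a criterion meant to judge a device that this participant never used for daily exercise.

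The decision to progress is the study's main product. If the criterion is applied literally, a failure says little about the device. If the team sets it aside once events are seen, no pre-set safety standard with a stated limit remains.

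**Working it through.** The article states no event rate, tolerated number or probability for this criterion, so there is no figure to reproduce.

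**Inputs from the article**

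- Total: "Sixty participants will be recruited" (Sample size justification), so n = 60.
- Allocation: "One-third of the participants will be randomised to the control condition" (Control condition), so 20 usual care and 40 exercise.
- Follow-up: "the final follow-up assessment will be conducted at 24 weeks" (Abstract, Methods).

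**Input assumed**

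- p, a participant's risk of at least one reportable event over 24 weeks. The article gives no value, so a range is shown. Participants are treated as independent with a common p.

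**Step 1. Chance of meeting the criterion as written.** There are zero reports only if no participant has an event, so P(zero) = (1 − p)^n. The n = 40 column shows what happens if only the exercise arms counted.

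| Assumed p | n = 60, all arms | n = 40, exercise arms |
|---|---|---|
| 0.5% | 74.0% | 81.8% |
| 1% | 54.7% | 66.9% |
| 2% | 29.8% | 44.6% |
| 5% | 4.6% | 12.9% |
| 10% | 0.18% | 1.5% |

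For example, 0.95^60 = 0.046 and 0.90^60 = 0.0018.

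**Step 2. Risk at which the criterion is an even bet.** Solve (1 − p)^n = 0.5, so p = 1 − 0.5^(1/n). This gives 1.15% for n = 60 and 1.72% for n = 40. For an 80% chance of passing with n = 60, p = 1 − 0.8^(1/60) = 0.37%.

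**Step 3. Contribution of usual care alone.** The chance of at least one affected participant among the 20 controls is 1 − (1 − p)^20. At 5% this is 1 − 0.358 = 64.2%; at 10% it is 1 − 0.122 = 87.8%. At these risks the criterion would more likely than not fail through participants who do no daily exercise with the ball.

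**Step 4. Sensitivity to loss from follow-up.** If 30% left and contributed no reports, 42 would remain (0.7 × 60). P(zero) is then 11.6% at 5% and 1.2% at 10%. The conclusion does not change.

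**Step 5. What zero would show if only related events counted.** For 0 of 40, the exact two-sided 95% upper limit is 1 − 0.025^(1/40) = 8.8%. Even a clean result in the exercise arms leaves a related-event risk of almost 9% compatible with the data.

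**The case against.** The strongest reply is that the article describes a judgement, not a mechanical rule. Two of the five criteria, willingness and acceptability, have no threshold, so the list cannot work as an all-must-pass test. The Sample size justification and the Discussion bring in other evidence. A reader might infer that one adverse event stops the programme; the article does not say so. This part of the reply stands. It leaves two different safety standards for one decision, and the stricter one is in the Analysis section.

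Second, the Outcomes and Analysis sections speak of *adverse incidents*, whereas the safety section speaks of *adverse events*, and nowhere are the two equated. If only device-related incidents were meant, p could be small and the criterion could be met: the 0.5% to 2% rows apply. This also stands as a limit on the claim. However, no section states that narrower meaning, and the Outcomes section simply counts reports.

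Third, a journal article condenses a fuller protocol, and grading of seriousness and causality is commonly left to that document. That is fair, and missing grading definitions are not the point here. The point is a criterion that the article states twice, with zero as its only passing value.

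Fourth, the event rate is an assumption. That is correct, and it is why the table starts at 0.5%. Entry requires medical stability, which lowers early risk. Whether all-cause risk over 24 weeks in this population exceeds 5% is plausible, but the article does not establish it.

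**Conclusion.** The criterion is unworkable as worded and should be fixed. On the literal all-cause, all-arm reading, it has less than a 5% chance of being met at any per-person 24-week risk of 5% or more. It is an even bet only if that risk is about 1.15%. Whichever way it falls, the result would be driven largely by background illness.

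This rests on three things: that *adverse incidents* covers the events reportable under the safety section, that participants are independent, and that the assumed risks are of the right order. A narrower meaning of the term would make the criterion attainable but would have to be written down.

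The stronger conclusion, that progression is bound to be blocked, does not follow, because no combining rule exists and the Discussion sets a softer standard. Allocation, sample size and the comparisons between arms are unaffected, and event reports with a description and outcome are already collected. That makes this a correction that should be made, not one that invalidates the study.

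**What to change.** Reconcile the Outcomes section, the Analysis section and the Discussion so that all three carry the same safety criterion. Replace the zero-incident wording with:

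- the number and proportion of participants in the two exercise arms with an adverse event judged related to the device or the exercise, serious and non-serious shown separately, with an exact 95% confidence interval;
- a tolerated number for that count, chosen by the study team before outcome data are reviewed by arm;
- all adverse events reported by arm as description, not as a criterion.

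Showing non-serious related events keeps discomfort or minor harm from the exercise within the progression decision, where a limit to serious events would drop them.

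The cost is a wording change, plus a relatedness item on the adverse event form if it does not already have one. There are three downsides. The criterion becomes less absolute. It depends on a judgement of relatedness in a trial where participants and the therapists who set exercise targets know the allocation. It would also be set after recruitment began on 08 June 2021 (Trial status); the report should say so and state that outcome data had not been reviewed by arm when the number was fixed.

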#### Videofluoroscopy

VF data will be analysed in two different ways: (1) The physiological effects of the chin tuck exercise rehabilitation intervention on the base of the tongue, posterior pharyngeal wall and laryngeal movement have not been fully clarified. Therefore, we will examine the changes in the movements of these three structures, with and without CTAR. (2) This data will be used as input to computational fluid dynamics simulations in order to determine the precise values of pressure, velocity, efficiency of bolus mixing and the stress exerted on the passage walls by the transiting bolus. This will establish the quantitative measures that will be important in establishing the repeatability of swallows and in evaluating the efficacy of the chin tick exercise.

## Discussion

A number of previous research studies have examined the interventions which aim to rehabilitate swallowing function through targeted strengthening of the suprahyoid muscles. The CTAR-SwiFt intervention builds on this literature, but also adds important novel aspects.

A swallow programme including strengthening exercises (Swallow-STRONG) which consist of tongue strengthening exercises [37] and the Shaker manoeuvre (neck exercises) [17] have been shown to improve swallow mechanics. Shaker and colleagues developed a system of ‘head raising’ exercises to strengthen the hyoid group of muscles and neck muscles [17]. The exercise programme is conducted in a supine position and consists of 3 head-raising exercises, held for 60 s each, followed by rapid neck flexion, for 30 times daily for 6 weeks. These exercises also involve activation of the anterior neck muscles (sternocleidomastoid) and abdominal muscles not directly related to swallowing. The exercise programme strengthens the suprahyoid muscles resulting in the improved upper esophageal opening (*p* < 0.01), laryngeal anterior excursion (*p* < 0.05) and reduction in post-swallow aspiration (*p* < 0.05) [17].

Mapani et al. [38] found that the Shaker exercise resulted in an increase in thyrohyoid shortening after 6 weeks compared to tongue exercises and swallowing manoeuvres. Some studies suggest that this type of exercise causes increased contraction pressure in the pharynx, increased pressures in the pyriform sinuses and shortened opening times of the UES. However, this is in contrast to some other studies [39, 40].

In frail older people, the Shaker exercise may not be technically feasible due to muscle weakness, fatigue or co-existing morbidities. Sze et al. [8] showed that it was possible to do this type of exercise by placing a partially inflated ball beneath the chin and then pressing down against the ball. This exercise—chin tuck against resistance (CTAR)—generated similar electromyography results and greater benefits than the Shaker exercise [35, 40]. Recently, Shaker and colleagues have suggested an alternative approach—‘laryngeal resistance’ [41].

The chin tuck is a swallowing exercise that is often deployed where the swallowing problem is secondary to a delay in the onset of the pharyngeal swallow. It is generally accepted that the exercise pulls the larynx up and forwards and at the same time opens the UES [17, 42]. Such a system is being utilised as part of the Ampcare neuromuscular stimulation programme [43, 44]. However, at present, it is not possible to perform the chin tuck exercise in a consistent way, with controlled effort because there is no means by which effort can be regulated by the patient. Moreover, Balou et al. [39] suggest that more data is required to determine how chin tuck affects the physiology of swallowing. The advantage of the chin tuck exercise, over the Shaker movement, is that the effects are more localised and less likely to unnecessarily recruit the large anterior muscles of the neck. Park et al. [45] studied stroke patients and showed positive clinical benefits of CTAR in a small randomised study.

Rogus-Pulia et al. [37] used isometric progressive resistance oropharyngeal therapy to demonstrate improved FOIS score (effect estimate 0.4, *p* < 0.02), reduced incidence of pneumonia and reduced number of hospital admissions, in a cohort that was mixed in aetiology of dysphagia. However, previous exercise interventions have not been carefully controlled. The ability to control one’s own effort during rehabilitation is essential in order to undertake the exercise in a consistent and regulated way, especially if it is to be performed by the patient at home. No exercise rehabilitation devices provide feedback that allows the patient to carefully control their effort when exercising at home. Furthermore, no previous exercise programmes allow logging of exercise data for subsequent review by the therapist in the clinic. The real-time feedback on exercise performance and the objective automated recording of completed exercises are important novel aspects of the CTAR-SwiFt swallowing exercise intervention.

As has been the case for much clinical research that is unrelated to coronavirus disease 2019 (COVID-19) [46], the COVID-19 pandemic has impacted the planning and conduct of this study also. Clinical services at the recruiting sites have continued with all non-elective care. Recruitment has therefore been impacted by the acuity of the presentation of the patients who have presented to and been admitted to hospital, resulting in a reduction in the expected patient population for the study. Patients who present with COVID-19 pneumonitis, a large proportion of admissions during the pandemic, are excluded from the study. Over the pandemic period, patients have had more rapid discharges from the hospital, resulting in a shorter period when patients who meet the study eligibility criteria are in hospital, and therefore, some suitable participants cannot be approached by the research team prior to discharge.

All follow-up appointments are taking place in the community or via telehealth (as opposed to initial plans of follow-up in a hospital outpatient clinic). The research team contact patients when their follow-up visits are due and ask whether they would prefer a home visit or telephone consultation. It should be noted that telephone consultations impact the data collection of the outcome measures TWTS and TUAG. Whilst these measures could be completed over a video call, the participants of this study have anecdotally expressed low levels of confidence using video calls. The timing of follow-up visits has also been impacted by researchers, patients or their families contracting COVID-19 or having to self-isolate.

Contingency plans include reduced recruitment target to the VF sub-group, as this requires attendance at the hospital for elective imaging. As VF can only be carried out in the hospital, this may also increase participant risk to exposure to COVID-19. A personal protective equipment (PPE) protocol has also been put in place for face-to-face follow-up visits, with researchers required to comply with the hospital PPE policy.

Future plans to continue this research will be based on findings from this study. A decision to proceed to a prospectively powered, definitive randomised controlled trial will be made according to feasibility outcomes, including recruitment and retention of study participants, participant compliance and acceptance of the CTAR-SwiFt intervention, and evidence of safety and potential effectiveness of the intervention. Aspects of the CTAR-SwiFt intervention and the trial design may be revisited according to learnings from this study. For example, it is acknowledged that this study protocol does not include any direct assessments of sarcopenia, such as imaging-based or invasive assessments of muscle mass, which were considered too burdensome for participants. The indicators that will allow the comparison of sarcopenia/frailty between the study groups are the Clinical Frailty Score, which is recorded as part of the eligibility screen, and the TUAG test. TUAG is a widely used measure in older clinical populations which incorporates lower limb strength (rising from the chair), gait speed and balance (180-degree turns), and it has been recommended for clinical assessment of sarcopenia [47]. Other similarly convenient and recommended clinical measures of sarcopenia, in particular, hand grip strength and anthropometric measurements such as calf and mid-upper arm circumference [47], may be considered in the design of a follow-up study.

## Conclusion

This study aims to evaluate the feasibility of conducting a definitive large-scale multi-centre trial of the CTAR-SwiFt intervention, a novel approach to exercise rehabilitation of the swallow using a feedback-enabled ball in combination with an Android application for smartphone or tablet. By improving the ability to swallow in frail older patients admitted to hospital with pneumonia, it is anticipated that patients’ oral intake will improve. It is suggested that this will further impact clinical, patient and healthcare economic outcomes, i.e. reduce the need for supplemental feeding, improve patient satisfaction with oral intake and swallowing-related quality of life, decrease the occurrence of chest infections and reduce hospital admissions and related healthcare costs.

